Participants attend baseline screenings, bi-weekly visits for the first two months, monthly visits until treatment completion, and quarterly check-ups during a 12-month post-treatment period (Tables S3 and S4). The screening procedures include medical history, physical examination, vision tests, peripheral neuropathy screening, psychological assessments, and the collection of various samples for testing. CT scans are preferred over X-rays for assessing lung lesions, which is a routine at the study sites.

Upon passing the screening, eligible participants are enrolled, registered offline, and assigned a treatment regimen by an authorized researcher at each sub-center. These assignments are re-verified by the Central Coordination and Quality Control Group (CCQCG) at Shenzhen Third People’s Hospital.

Effectiveness and safety metrics are evaluated at each follow-up visit through symptom checklists, clinical exams, and ongoing diagnostic tests. Grade 3 or 4 clinical and laboratory adverse events (AEs) are defined per the DAIDS AE Grading Table [12]. Chest CT scans are regularly updated and reviewed blindly by two independent experts using a standardized approach (Table S2). An endpoint review committee examines unfavorable clinical outcomes like treatment failure, TB recurrence, or death. Adherence metrics and educational counseling are also provided, along with psychological support through WeChat and telephone channels. Post-treatment, successfully treated cases will be monitored for 12 months to assess any TB recurrence.

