### Outcome measures

In this study, outcomes are categorized at the end of a 12-month post-treatment follow-up. Participants fall into one of three categories: unfavorable outcome, favorable outcome, or not assessable - the latter are excluded from the primary analysis (Table S7). The primary efficacy outcome, determined 15 months after initial assignment, includes treatment failure, loss to follow-up, or death from any cause. Treatment failure is a multifaceted term, defined by the end-point review committee, and encompasses lack of clinical and/or bacteriological response, adverse drug reactions that induced regimen adjustments, or newly identified drug resistance. Specifically, bacteriologic failure is defined by the presence of two genetically identical, *M. tuberculosis*-culture-positive sputum samples within the month 8 visit window. Bacteriologic relapse and reinfection refer to a positive test for a genetically identical or different *M. tuberculosis* strain, respectively, within 12 months post-treatment. In cases where strain genotyping is not feasible, the term ‘bacteriologic recurrence’ is employed. Secondary efficacy outcomes include unfavorable status at 21 months post-assignment, end-of-treatment success, culture conversion by month 2, time to sputum culture-negative status in liquid media, and favorable treatment response at FR-6. Safety outcomes involve the occurrence of AEs graded ≥ 3 or serious AEs of any grade within 6–9 months of treatment initiation, as per the DAIDS AE Grading Table [15]. Clofazimine-induced skin discoloration is also specifically documented (Table S2).

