### Sample size calculation

Group A/B in the randomized withdrawal trial: According to a 2018 IPD meta-analysis [7] and our previous study [14], we assumed that two groups (A and B) have an assumed favorable outcome rate of 73%. Taking into consideration various parameters like a 90% FR-6 rate, a 1:1 random assignment to two different durations (month 6 or month 9), a 15% margin of non-inferiority, a one-sided significance level of 5%, 80% power, and a 20% drop rate, 304 participants are needed for each group. Hence, 304 + 304 = 608 participants in total for groups A and B.

Calculation for Group C/D in the single-arm trial: Two other groups (C and D) have an assumed favorable outcome rate of 57% [7, 14]. Using the same parameters (15% margin of non-inferiority, a one-sided significance level of 5%, 80% power, and a 20% drop rate), 85 participants are needed for each group. Hence, 85 + 85 = 170 participants in total for groups C and D.

Combining both sets of groups, the total sample size required would be 608 + 170 = 778 participants for the SEAL-MDR study.

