### Statistical analysis

Efficacy outcomes will be evaluated using modified intention-to-treat (mITT) and per protocol (PP) approaches, focusing on mITT. The safety analysis includes all participants receiving at least one dose of study drugs. The mITT group consists of those randomized and treated at least once, while the PP group comprises mITT members who complete > 80% of planned treatment and adhere to the protocol.

Analysis is performed in SPSS 26.0. Categorical data are presented as counts and percentages, and continuous data as means (standard deviations, SD) and medians (interquartile range, IQR). Depending on data distribution, Student’s t-test or non-parametric tests are used for continuous variables, and Chi-square or Fisher’s test for categorical ones. Primary analysis estimates unfavorable outcome rates in subgroups of Regimens A and B, with 95% CI for each group. Kaplan-Meier and Cox models evaluate time to unfavorable outcomes and culture conversion. Variables with *P* < 0.1 in univariate analysis and clinical significance are incorporated into a multivariate model. A *P* < 0.05 is considered significant.

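### The primary 6- versus 9-month comparison names no covariate although month-6 randomisation makes earlier response data legitimate baseline covariates: a small missed efficiency, not an error

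*Protocol article*

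**What the plan says.** The primary analysis is stated in the protocol article under Statistical analysis: "Primary analysis estimates unfavorable outcome rates in subgroups of Regimens A and B, with 95% CI for each group". The only text on covariates comes two sentences later, after the Kaplan-Meier and Cox models. It admits variables to a multivariate model by a univariate P below 0.1 together with clinical significance, and does not link that model to the primary analysis.

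Under Randomization, enrolment and follow-up, participants are randomised to 6 or 9 months only after a month-6 review has found a favourable response (FR-6). That review covers culture conversion at month 4, drug intake of roughly 90% or more, and stable chest CT. The same section says of imaging: "Chest CT scans are regularly updated and reviewed blindly by two independent experts using a standardized approach". Under Outcome measures, early culture response appears only among the secondary efficacy outcomes: "culture conversion by month 2, time to sputum culture-negative status in liquid media".

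The Sample size calculation section gives the planning values for Regimens A and B: "we assumed that two groups (A and B) have an assumed favorable outcome rate of 73" per cent, "a 1:1 random assignment to two different durations (month 6 or month 9"), "a 15% margin of non-inferiority", "a one-sided significance level of 5" per cent, and "80% power, and a 20% drop rate, 304 participants are needed for each group".

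**The concern.** In a trial randomised at the start of treatment, month-2 culture status and time to conversion are post-randomisation variables, and adjusting for them could bias the comparison. Here allocation comes at month 6, so they cannot be affected by the duration assigned and count as baseline. The same holds for CT readings made before randomisation. A patient who converted by month 2 and one who converted at month 4 can both pass FR-6, and stable CT can mean limited or extensive disease. Some prognostic variation may therefore remain among those randomised.

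Each regimen is sized for 80% power on its own. Adjusting the risk difference for prognostic pre-randomisation variables can narrow its interval and account for chance imbalance, with no extra participants, visits or tests. What is at stake is a few points of power in each regimen.

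**Working it through.** **Inputs from the article (Sample size calculation).** Favourable rate 0.73 in both arms (unfavourable 0.27); margin 0.15; one-sided alpha 0.05; power 0.80; FR-6 rate 0.90; drop-out 0.20; allocation 1:1.

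**Reproducing the stated size.**
- Per arm: n = 2 × 0.73 × 0.27 × (1.645 + 0.842)² / 0.15² = 108.3, rounded up to 109.
- Randomised and evaluable per regimen: 2 × 109 = 218.
- Allowing for FR-6: 218 / 0.90 = 242.2, rounded up to 243.
- Allowing for drop-out: 243 / 0.80 = 303.75, rounded up to **304**, which matches the article.

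This is an unadjusted two-proportion formula, so the sizing does not rely on adjustment.

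**Power as planned.** SE of the difference = √(2 × 0.73 × 0.27 / 109) = 0.0601. Power = Φ(0.15 / 0.0601 − 1.645) = **80.2%**.

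**Effect of adjustment.** Let v be the ratio of adjusted to unadjusted variance. Then power = Φ(0.15 / (0.0601 × √v) − 1.645), and the n per arm for 80% power is 108.3 × v, rounded up. The article does not say how strongly month 0–6 data predict the outcome, so v has to be assumed. The values below come from 6,000 simulated trials per scenario: 109 per arm, no true difference, 27% unfavourable, and three binary covariates with prevalence 30%, 50% and 25%.

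| Assumed odds ratios | v | Power by formula | Gain (points) | n per arm for 80% |
|---|---|---|---|---|
| none (unadjusted) | 1 | 80.2% | – | 109 |
| 1.5, 1.5, 1.5 | 0.998 | 80.3% | 0.1 | 109 |
| 2, 2, 2 | 0.967 | 81.4% | 1.2 | 105 |
| 3, 3, 2 | 0.903 | 83.6% | 3.4 | 98 |

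The half-width of a 95% interval for the difference is 1.96 × 0.0601 × √v: 11.8 points unadjusted, 11.6 at v = 0.967 and 11.2 at v = 0.903.

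**Why the formula and not the simulated power.** The simulated powers (unadjusted, then adjusted) were 80.9% and 81.3%, 79.3% and 81.3%, and 81.3% and 84.8% in the three scenarios. Part of those gains is not precision: with three covariates at this sample size, the influence-function SE runs about 2% below the empirical standard deviation, which slightly flatters adjusted power. The formula uses only the variance ratio.

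**A single covariate, for scale.** Taking v = 1 − R², a binary factor with 20% to 30% prevalence that doubles the risk has R² of about 0.04 to 0.05 and adds about 1.5 to 2 points of power. One that triples the risk has R² of about 0.12 and adds about 4 to 5 points, but that is a strong effect to expect in a group already selected for response.

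**The case against.** The strongest case against is that the article contains no error here. A randomised comparison without covariates is unbiased, its interval already allows for chance imbalance, and 80% power is a conventional target that the stated sample size meets. All of that stands.

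A reader might infer that the plan rules out adjustment. It does not: it is silent on covariates for the primary analysis, its multivariate model has no stated scope, and an analysis plan that is not shown may add a covariate list. What can be said is that the article chose to state a primary estimator, and that estimator is crude.

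A reader might also infer that six months of prognostic data are being thrown away. The documents do not support that. FR-6 makes month-4 conversion, drug intake and CT stabilisation nearly constant among those randomised, and time to conversion is largely cut off at month 4. The primary outcome also counts loss to follow-up, death from any cause and regimen changes for adverse reactions, and nothing in the article shows that early culture or CT findings predict that composite in selected responders. The no-gain scenario is therefore realistic.

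Finally, the article names no cavitation or extent-of-disease item. It refers to a standardised CT approach in a supplementary table that is not shown, so whether such a covariate is available has to be checked.

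These points limit the size of the finding. They do not remove it: the timing of randomisation does make these variables legitimate covariates, and the stated primary analysis does not use them.

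**Conclusion.** The point holds as a small missed efficiency and not as an error, a bias or a shortfall in sample size. Adjustment would raise power from 80.2% to between about 81% and 84% if it reduces the variance by 3% to 10%, and would add nothing if the covariates are weakly prognostic. These figures rest on the article's planning values, on 109 evaluable participants per arm, on a one-sided 5% test, and on assumed prognostic strengths that the article cannot confirm. The improvement is optional but cheap.

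**What to change.** Within each of Regimens A and B, define the primary estimate as the 6-minus-9-month difference in the risk of an unfavourable outcome, standardised from a logistic model. This stays on the same absolute scale as the margin, and it supplies the between-duration contrast that an interval for each group does not give.

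- **Covariates:** a short list fixed in advance, with no P < 0.1 screening. Use month-2 culture status, plus an extent-of-disease item from the pre-randomisation CT reading if the standardised form records one.
- **Standard error:** robust or bootstrap, with coverage checked by simulation at about 109 per arm.
- **Decision:** compare the confidence limit with the 15-point margin, at a stated level consistent with the sizing.
- **Sensitivity analysis:** the unadjusted risk difference.

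The cost is analysis wording, a little more programming, and a rule for missing month-2 cultures (for example a missing-indicator category). No additional participants, visits or tests are needed.

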### Randomization, enrolment and follow-up

Before initiating treatment, all available DST results (e.g., Xpert, gDST, pDST) are employed to triage patients with MDR-TB and pre-XDR-TB. Considering variables such as regimen affordability and past adherence, MDR-TB patients are allocated to either Regimen A or B (Table 1). Regimen B is preferred for uninsured participants, those concerned about drug costs, and individuals willing to accept potential skin discoloration caused by Cfz. Pre-XDR-TB patients are allocated to either Regimen C or D, with Regimen D being better suited for those without insurance coverage and lesser financial means.

Should post-entry DST results confirm resistance to any study drug, treatment regimens will be adjusted according to established clinical practice principles in our previous studies [1]. For example, If initial gDST is unavailable and later pDST reveals FQ resistance 2–3 months post-enrollment, participants will transition from Regimens A/B to C/D, incorporating the prior treatment duration into the revised 6-month course. In certain scenarios, participant withdrawal may be necessitated. For example, participants unwilling to switch sill be prescribed long-course treatment and excluded from the study.

Participants initially undergo a 6-month treatment course. A blinded mid-point review committee evaluates clinical events and favorable treatment responses during the sixth-month visit (FR-6, Table S2). This assessment includes sputum culture conversion at month four, adequate drug intake at month six (excluding those who received less than ~ 90% of study doses), and chest computed tomography (CT) stabilization. Participants having a FR-6 will be centrally randomized into either a 6- or 9-month treatment group via MedSci RTSM Cloud Platform (rtsm.medsci.cn). Otherwise, they will continue their current regimen until month nine. Failure to convert by the eighth month necessitates an extension to an 18–20 month regimen, marking it as a treatment failure.

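### Kaplan-Meier is named for time to culture conversion, an event that death precludes; if deaths are censored, the curve modestly overstates the proportion converting outside the randomised A/B set

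*Protocol article*

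**What the plan says.** In the protocol article, Statistical analysis, one sentence covers both time-to-event endpoints: "Kaplan-Meier and Cox models evaluate time to unfavorable outcomes and culture conversion". It names no competing-risk method and does not say how a death before conversion is treated.

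Under Outcome measures, the primary efficacy outcome "includes treatment failure, loss to follow-up, or death from any cause". The secondary efficacy outcomes include "culture conversion by month 2, time to sputum culture-negative status in liquid media, and favorable treatment response at FR-6". Death is therefore an event in the first endpoint and not in the second.

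Two further statements determine where the issue can arise. On the main efficacy set, Statistical analysis says "The mITT group consists of those randomized and treated at least once". On who is randomised, Randomization, enrolment and follow-up says "Participants having a FR-6 will be centrally randomized into either a 6- or 9-month treatment group", and of the FR-6 review it says "This assessment includes sputum culture conversion at month four, adequate drug intake at month six". Groups C and D are not randomised; Trial design and oversight leaves their duration to clinical judgement.

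**The concern.** Kaplan-Meier has two states for each participant: event observed, or censored and assumed still able to have the event later. For time to unfavourable outcome that works, because death counts as the event. For conversion, censoring a death passes that patient's weight to those still at risk, as though the dead patient would have converted at the same rate. One minus the estimate then describes conversion in a setting where nobody dies, not the share of treated patients who convert.

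What is at stake is the descriptive conversion curve. It matters most where there is no concurrent randomised control, as in Groups C and D with 85 participants each, because a reader may take the plotted proportion at face value or compare it with published figures. The curve would not penalise a regimen for deaths that occur before conversion.

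**Working it through.** **The plan's own figures.** The article states no figure for time to conversion or for deaths before it, so there is nothing to reproduce on this point. The sample sizes rest on favourable-outcome rates and do not use the conversion curve:
- A and B: 2 × 0.73 × 0.27 × (1.645 + 0.842)² / 0.15² gives 109 per arm, 218 for two arms; 218/0.9 gives 243; 243/0.8 gives 304.
- C and D: 0.57 × 0.43 × (1.645 + 0.842)² / 0.15² gives 68; 68/0.8 = 85.

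Both agree with Sample size calculation and neither depends on how conversion is analysed.

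**Where the overstatement can arise.**
- *Randomised A and B:* entry to randomisation needs FR-6, which includes conversion at month four and is judged at the month-six visit. Everyone in the set has converted and is alive at month six. No death precedes conversion, so the overstatement is exactly zero.
- *All enrolled A and B:* some can die unconverted, so it can arise.
- *C and D:* not randomised and not selected on conversion, so it can arise. The mITT definition, which requires randomisation, gives these groups no analysis set.

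**Size.** All rates here are assumptions, because the article gives no death rate for any trial group. Take constant hazards, c for conversion and d for death, with no other censoring and t in months:
- 1 − KM with deaths censored = 1 − exp(−c·t)
- cumulative incidence = c/(c + d) × [1 − exp(−(c + d)·t)]

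Set c so that 1 − KM is 85% at month 4: c = −ln(0.15)/4 = 0.4743. For 5% six-month mortality, d = −ln(0.95)/6 = 0.00855. Cumulative incidence at month 4 is then 0.4743/0.4828 × [1 − exp(−1.931)] = 0.9823 × 0.8550 = 0.840.

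| Six-month mortality (assumed) | 1 − KM, month 4 | Cumulative incidence, month 4 | Overstatement (points) | Deaths before conversion by month 4, per 85 |
|---|---|---|---|---|
| 2% | 85.0% | 84.60% | 0.40 | 0.5 |
| 5% | 85.0% | 83.99% | 1.01 | 1.3 |
| 10% | 85.0% | 82.95% | 2.05 | 2.6 |
| 15% | 85.0% | 81.86% | 3.14 | 4.0 |

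Letting month-4 conversion run from 75% to 95% barely changes this: about 0.4 points at 2% mortality, 0.9 to 1.0 at 5%, 1.9 to 2.0 at 10%, and 2.8 to 3.1 at 15%.

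**The one mortality figure in the article.** The Introduction gives 30–50% as background for MDR-TB and pre-XDR-TB together, with no time window and no split by group. If it applied in full, the month-4 overstatement would be 1.8 to 3.8 points with deaths spread over 21 months, and 4.1 to 8.5 points if all fell within 9 months. Nothing in the article says that it describes the trial's patients.

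**Against sampling error.** With 85 participants and 85% converting, the standard error is √(0.85 × 0.15/85) = 0.039, or 3.9 points. The overstatement stays below one standard error throughout the table.

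**The case against.** The strongest reply is that the article never says deaths are censored. If deaths stay in the risk set as non-converters to the end of the window, the overstatement disappears, and such a rule is commonly left to a statistical analysis plan that is not shown. This stands in part: censoring is the ordinary use of the named method, not a stated rule. But the article does more than stay silent. It names an estimator for this endpoint, in the same sentence as an endpoint with a different structure, and gives no sign that the two are handled differently.

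A second reply is that conversion by month 2 and the FR-6 rate are separate secondary outcomes that need no Kaplan-Meier estimate. That is right, and it limits the issue to the time-to-conversion curve, defined as "time to sputum culture-negative status in liquid media".

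A reader might infer three stronger things that the document does not support:
- *That the overstatement is largest in C and D because more of those patients die.* The article says "Two other groups (C and D) have an assumed favorable outcome rate of 57" percent, which leaves 43% unfavourable. That share also contains treatment failure and loss to follow-up, so it is not a death rate. The reason C and D are exposed is structural: they are not selected on having converted.
- *That more early deaths make a regimen look better.* In the formula above, 1 − exp(−c·t) does not contain d. Deaths do not raise the curve; they are simply not penalised.
- *That the size reaches about 6 points.* For example, 75% converting and 10% dying first by month 6 gives 1 − KM = 1 − exp(−1.897 × 0.75/0.85) = 81.2%. But it implies six-month mortality of 1 − exp(−1.897 × 0.10/0.85) = 20%, for which the article gives no basis in any trial group.

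**Conclusion.** The point holds as a minor one. Kaplan-Meier with deaths censored is the wrong estimator for the proportion converting, and a better one is readily available. The overstatement at month 4 is about 0.4 to 2 points for 2% to 10% six-month mortality, and about 3 points at 15%. It is zero among randomised A and B participants, and possible in C and D and in all enrolled A and B participants.

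This rests on deaths being censored in the usual way, on constant hazards, on no other censoring, and on assumed conversion and death rates. Only the descriptive curve of a secondary outcome is affected. A Cox model that censors deaths still estimates the cause-specific hazard of conversion.

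**What to change.** In Statistical analysis, split the sentence in two. Keep Kaplan-Meier for time to unfavourable outcome. For culture conversion, state that all participants who started treatment are analysed, that time runs from treatment start, and that the Aalen-Johansen cumulative incidence is reported with death as a competing event. Describe the Cox model as cause-specific.

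A simpler alternative is to keep deaths in the risk set as non-converters to the end of the conversion window. This gives the same answer when nobody is otherwise censored before the window closes, and is approximate if some are.

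The cost is a sentence or two, a slightly lower reported conversion proportion, and possibly a routine outside SPSS 26.0, the only software the article names.

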## Methods

### Trial design and oversight

We are conducting a two-part, patient-stratified, treatment-response-guided study: a randomized withdrawal trial for MDR-TB and a single-arm trial for pre-XDR-TB (Fig. 1; Table 1). For MDR-TB, patients are assigned to either Regimen A (Bdq, Lzd, Mfx, Cs) or Regimen B (Lzd, Mfx, Cs, Cfz, Pza) based on treatment preference and FQ drug susceptibility tests (DST). Compared to our previous study, Pza is deleted from Regimen A. For pre-XDR-TB, we employ Regimen C (Bdq, Lzd, Cs, Cfz, Pza) and Regimen D (Lzd, Cs, Cfz, Pza, SASP). Each regimen lasts 6–9 months. Post-6 months, participants in Groups A and B are subdivided into 6-month and 9-month treatment durations based on randomization, while those in Groups C and D are similarly divided based on clinical judgment. For the randomized withdrawal trial, the primary hypothesis is that the 6-month regimen will be non-inferior to the 9-month regimen in terms of unfavorable outcomes.

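### Covariates for the multivariable models are screened by univariate P < 0.1, so P values for retained variables are over-optimistic, and the randomised duration is not guaranteed a place in the model

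*Protocol article*

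**What the plan says.** All statements are in the protocol article.

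- **Models (Statistical analysis):** "Kaplan-Meier and Cox models evaluate time to unfavorable outcomes and culture conversion".
- **Selection rule (next sentence):** variables with univariate P < 0.1 "in univariate analysis and clinical significance are incorporated into a multivariate model". The text does not say whether a variable must meet both criteria or whether either is enough.
- **Threshold (same section):** P < 0.05 "is considered significant". Sidedness is not given.
- **Primary analysis (same section, stated separately):** "Primary analysis estimates unfavorable outcome rates in subgroups of Regimens A and B, with 95% CI for each group". No covariate model is attached to it.
- **Randomised factor (Randomization, enrolment and follow-up):** "Participants having a FR-6 will be centrally randomized into either a 6- or 9-month treatment group".
- **Hypothesis (Trial design and oversight):** "the primary hypothesis is that the 6-month regimen will be non-inferior to the 9-month regimen in terms of unfavorable outcomes".

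Nothing says that duration is one of the screened variables, and nothing says that it is always kept.

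**The concern.** Two things can go wrong in the multivariable models.

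1. A variable enters because its P value on these data was small. The refitted model then tests it on the same data as if it had been chosen in advance. Its P value and confidence interval ignore the selection, so a reader will trust the listed predictors more than is warranted.

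2. In a non-inferiority trial the randomised factor is expected to show little difference. A rule that admits variables on a small univariate P value works against that factor in the scenario the trial is planned for. If duration is subject to the rule, the adjusted model for time to unfavourable outcome may contain no duration estimate.

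**Working it through.** **Inputs.** From Sample size calculation: 73% favourable (27% unfavourable), 15-point margin, one-sided 5%, 80% power, 90% FR-6 rate, 20% dropout, 1:1 allocation, 304 per regimen. Assumed here: two-sided screening P values, 10 or 20 candidate covariates, pairwise correlation 0 or 0.3. The article gives neither a candidate list nor correlations.

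**Step 1: the plan's own figure.** Per arm, n = 2 × 0.73 × 0.27 × (1.645 + 0.842)² / 0.15², which rounds up to 109. Then 109 / 0.9 / 0.8 = 151.4, rounded up to 152, and 2 × 152 = 304. The stated size is reproduced, and the covariate rule plays no part in it. It leaves 2 × 109 = 218 evaluable per regimen and 218 × 0.27 ≈ 59 events.

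**Step 2: P values after the screen.** For a single null variable, P(P < 0.05 given P < 0.1) = 0.05 / 0.10 = 50%. With several candidates the refit changes this, so Cox models were simulated (800 runs per setting, n = 218, no true effects, screen at P < 0.1, then refit):

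| Candidates, correlation | Retained nulls with P < 0.05 | Rate over all candidates, screened | Rate over all candidates, full model without screen |
|---|---|---|---|
| 10, r = 0 | 50% | 5.1% | 6.0% |
| 10, r = 0.3 | 27% | 2.8% | 6.2% |
| 20, r = 0.3 | 21% | 2.1% | 6.8% |

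The excess over the nominal 5% lies in the second column, among the variables that are retained and reported. With Wald tests, P < 0.05 is the same event as a 95% interval that excludes a hazard ratio of 1, so the same percentages apply to the intervals of retained null variables.

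**Step 3: duration, if it must pass the screen.** On the risk scale with 109 per arm, for an excess d over 27%: SE = √[(0.27 × 0.73 + (0.27 + d)(0.73 − d)) / 109], and P(dropped) = Φ(1.645 − d/SE) − Φ(−1.645 − d/SE).

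- d = 0: 90% (simulation 88% to 91%)
- d = 5 points: SE = 0.0617, dropped 79%
- d = 10 points: SE = 0.0628, dropped 52%
- d = 15 points: SE = 0.0636, d/SE = 2.36, dropped 24%

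On the hazard scale, d/SE is replaced by √(E/4) × ln(HR), with E the number of events. With 59 events in one regimen, duration is dropped in 82% of trials at HR 1.2, 73% at 1.3 and 53.5% at 1.5. With A and B pooled (118 events) the figures are 74%, 59% and 29%. With no true difference it is 90% either way. At the margin, HR = ln(0.58)/ln(0.73) = 1.73 with 109 × 0.27 + 109 × 0.42 ≈ 75 events, which gives 23%, in line with the risk-scale result.

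**Step 4: which model needs duration.** FR-6, the condition for randomisation at month 6, includes culture conversion at month four. Conversion therefore largely precedes randomisation, and duration matters only for time to unfavourable outcome.

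**The case against.** The strongest reply has four parts.

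- **The rule has a second criterion.** If clinical significance alone admits a variable, duration and known prognostic factors can enter whatever their P value. This stands: the drop-out figures for duration hold only if both criteria are required and duration is among the screened variables.
- **Silence is not exclusion.** A condensed article may leave the covariate list and the place of the treatment term to the analysis plan. This stands as far as dropping is concerned: it is possible, not stated. It does not excuse the P < 0.1 screen, which the article does state.
- **The screen does not create more false predictors.** A reader might infer that it does, because at least one null covariate came out significant in 22%, 39% and 52% of simulated trials with 5, 10 and 15 independent candidates (4,000 datasets each, linear-model approximation). Testing that many variables with no screen gives 1 − 0.95^k = 23%, 40% and 54%. Those figures show ordinary multiplicity, and the table above shows no inflation over all candidates. This part of the reply is right.
- **The primary comparison is untouched.** A reader might infer that the non-inferiority result is at risk, or that the adjusted model is meant to support it. The article says neither. The primary analysis consists of outcome rates with confidence intervals and uses no covariate selection.

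**Conclusion.** The point holds for the secondary multivariable models and is minor to moderate. What is firm is that the screen is a stated rule and that P values and intervals reported after it are over-optimistic for the retained variables: 21% to 50% of retained null variables reach P < 0.05. That range rests on the assumed number and correlation of candidates. It also takes the selection sentence to refer to the Cox models named just before it, which is the natural reading but is not spelled out.

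What is conditional is the loss of duration: about 90% with no true difference and about 24% at the full margin, given 109 per arm, a 27% unfavourable rate in the reference arm, and a requirement that duration itself reach P < 0.1. The documents do not support saying that duration will be dropped. They support only saying that its place in the model is not secured.

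**What to change.** Amend the Statistical analysis text, or settle the matter in the analysis plan before data lock:

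- Drop the P < 0.1 screen.
- Pre-specify the adjustment covariates on clinical grounds, from baseline data the trial already collects (screening covers medical history, examination and imaging of lung lesions).
- Always include randomised duration in the models for time to unfavourable outcome among randomised Regimen A and B participants, and include regimen or stratify by it.
- Do not require duration in the culture-conversion model.
- Label any data-driven search for predictors as exploratory.

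This costs wording only. It needs no new data or participants, and 304 per regimen does not change. The chance that duration is left out of the model falls to zero.
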